#### *1.1.1 Conceptual framework*

The modified socioecological framework outlines the four interacting levels of personal and environmental factors that impact maternal and child health. The structural level refers to systems that evoke socioeconomic/cultural policies and norms; the community level pertains to care settings and resources that impact women's access; the interpersonal level is personal relationships; and the individual level is a woman's physical and mental health. Based on the framework and relevant literature, we hypothesize that, compared to CPSP/IC, Glow/GC has greater capacity to improve mental health (primary aim), result in more positive care experience (secondary aim) and decrease PTB rates (exploratory aim) by incorporating social determinants of health, peer-to-peer processes, and process-of-care factors (see Figure 1).

Figure 1. Conceptual Framework

[figure not shown]

## 2.0 STUDY HYPOTHESES AND DESIGN

This randomized comparative effectiveness trial has three aims and each has primary and secondary hypotheses.

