| TITLE:                | Engaging Mothers & Babies – Reimagining Antenatal Care for Everyone (EMBRACE)                                                                                                                                                                                                                                                                                                                                                                                                                                                                                                                                                                                                                                                                                                                                                                                                                                                                                                                                                                                                                                                              |
| Primary objectives:   | 
To determine whether pregnant individuals allocated to receive group prenatal care with wrap around services (Glow/GC; administered by First 5 Fresno County) versus pregnant individuals allocated to receive individual prenatal care with supplemental services covered by the California Department of Public Health Comprehensive Perinatal Services Program (CPSP/IC).
 

1. Have greater reductions in depressive symptom severity

2. Report more person-centered care

3. Have lower rates of preterm birth (exploratory)

                                                                                                                                                                                                                                                                                                                                                                                                                                                                                                                                       |

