## **7.2 Sample Size**

We conducted sample size calculations for change in depressive symptom severity. We powered our study to detect meaningful changes in depressive and anxiety symptoms. Using an alpha of .05 and power of .85, we will be able to detect a standardized effect size of 0.25 with a sample size of 578 individuals in total (289 per arm). We are assuming a retention rate of 88% (as per our previous study and experience in the current study) and power of 85% (per PCORI's request). A standardized effect size of 0.2 to 0.3 is widely considered to be a small effect size. We therefore plan to enroll 657 participants in the study, and, with a retention rate of 88%, we will have > 85% power to detect small effect sizes for these outcomes. Adjustment for covariates in multivariable analyses for numeric outcomes may make the residual SD smaller than the raw SD, improving precision and power.

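### The plan contradicts itself on whether person-centered care is a primary or a secondary aim, and no testing rule says which result decides the trial

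*Combined protocol and SAP*

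**What the plan says.** **Where both aims are primary.** Section 2.0 states: "This randomized comparative effectiveness trial has three aims and each has primary and secondary hypotheses". Section 2.1 gives Aim 1 a primary hypothesis (PHQ-9 reduction at 3 months postpartum) and Aim 2 a primary hypothesis (person-centered care in the third trimester). Only Aim 3 is called exploratory. The Study Schema agrees: its primary objectives include "Report more person-centered care" next to depressive symptom severity, and only preterm birth is marked exploratory.

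**Where they are ranked.** Section 1.1.1 expects Glow/GC to "improve mental health (primary aim), result in more positive care experience (secondary aim) and decrease PTB rates (exploratory aim"). The version 3 entry in section 10.0 likewise describes mental health as having become the primary aim.

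**What is said about error rates.** Section 7.2 says: "Using an alpha of .05 and power of .85, we will be able to detect a standardized effect size of 0.25". That calculation is for depression: "We conducted sample size calculations for change in depressive symptom severity". Section 7.5 gives no order of testing between aims, no division of alpha, and no statement on the standing of the secondary hypotheses. The only other threshold is p < .10 for the interaction tests of treatment heterogeneity.

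**The concern.** A reader cannot tell which result decides whether the trial is positive. Under 1.1.1 it is depression alone. Under the schema and 2.1, person-centered care also carries the primary label. Because 7.5 is silent, a failed depression test followed by a significant person-centered care result could be reported as a confirmed primary hypothesis for Glow/GC.

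That matters for three reasons. The sample size was calculated for depressive symptoms, with no calculation for care experience. The Aim 2 scale is the participant's own rating of the care being compared, and section 7.4 says participants know their assignment. Section 8.5 expects the findings to inform policy makers and payers on expanding group care, so what counts as proof should be fixed before the data are seen.

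**Working it through.** **1. Reproduce the sample size and identify the test behind it.** Inputs from 7.2: alpha .05, power .85, standardized effect 0.25, retention 88%.

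- Per arm, normal approximation, two-sided: n = 2(1.960 + 1.036)² / 0.25² = 287.3, so 288. The t-test version gives 288.3, so 289 per arm and 578 in total. This matches "with a sample size of 578 individuals in total (289 per arm").
- Enrolled: 578 / 0.88 = 656.8, so 657, as stated.
- One-sided .05 would need only 230.7 per arm, so the stated figure implies a two-sided test.
- Power with 289 per arm is 85.1% (t-test).

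The 289 per arm therefore corresponds to one two-sided .05 test of change in depressive symptoms.

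**2. Count the non-exploratory primary hypotheses.** Section 2.1 has two: PHQ-9 at 3 months postpartum and person-centered care in the third trimester.

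**3. Chance of at least one false primary result.** Assume both nulls are true, each hypothesis is tested at two-sided .05, and either may support a claim.

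- Independent tests: 1 − (1 − 0.05)² = 0.0975.
- Correlated tests: 1 − P(|Z₁| ≤ 1.96 and |Z₂| ≤ 1.96), with Z₁ and Z₂ bivariate normal with correlation ρ.
- Counting only false results in favor of Glow/GC: 1 − P(Z₁ ≤ 1.96 and Z₂ ≤ 1.96). At ρ = 0 this is 1 − 0.975² = 0.0494. A single test gives 0.025.

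The documents give no correlation between the two outcomes, so ρ is an assumption and is shown as a range:

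| ρ | False result in either direction | False result favoring Glow/GC |
|---|---|---|
| 0 | 9.75% | 4.9% |
| 0.5 | 9.1% | 4.5% |
| 0.8 | 7.8% | 3.9% |
| One test only | 5% | 2.5% |

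**4. Compare two ways of controlling this.**

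- *Split alpha, .025 each.* Under independence the overall rate is 1 − 0.975² = 4.9%. Power for depression with 289 per arm falls from 85.1% to 77.6% (t-test). By the normal approximation, restoring 85% needs 688 evaluable, and 688 / 0.88 = 781.8, so 782 enrolled.
- *Fixed sequence, depression first.* Depression keeps the full two-sided .05, so its power stays at 85% and enrollment at 657. The Aim 2 primary hypothesis is tested at .05 only if depression is significant, which holds the error rate for the pair at 5%.

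**The case against.** The strongest reply is that the plan does rank its outcomes. Section 1.1.1 orders the aims, sections 2.1 and 7.5 label outcomes and time points as primary or secondary, and the sample size is tied to depression. This stands, and it would be wrong to say the plan has no hierarchy. What is missing is a testing rule that uses the ranking, and the schema and 2.1 conflict with it.

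Second, testing every hypothesis at .05 is inferred from silence. The .05 is a sample-size input and is nowhere set as a family-wise limit. This also stands, so the figures above are conditional: they describe what the plan allows, not a breach of a limit it set.

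Third, the hypotheses favor Glow/GC, and about half of the two-sided errors would favor CPSP/IC. That is correct and is why the table shows both bases. The relative inflation over a single test remains on either one.

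Fourth, symptoms and care experience are different questions, and treating the aims as separate families is defensible in a comparative effectiveness trial. But the plan does not declare that position, and it would fit poorly with the ranking in 1.1.1.

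A reader might also pool the seven secondary hypotheses of Aims 1 and 2 with the two primaries and infer a much larger error rate. Nine independent tests give 1 − 0.95⁹ = 37.0%, and a common correlation of 0.8 gives 16.6%. The documents do not support that as a finding. No section says the secondaries will be claimed as confirmatory, section 7.5 promises estimates with confidence intervals for all analyses, and the count itself depends on which list of time points is used (section 7.1 lists more contrasts than 2.1).

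**Conclusion.** The point holds as a contradiction with a missing rule. The schema and 2.1 give person-centered care primary standing, and 1.1.1 makes care experience secondary. The entry in section 10.0 points the same way as 1.1.1, but the contradiction does not rest on it. Nothing in 7.2 or 7.5 settles which result decides the trial.

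The error rates in the table rest on three assumptions: both hypotheses are tested at two-sided .05, either one can support a claim, and the correlation between the tests lies between 0 and 0.8. The change is worth making before analysis because it settles what a positive trial means, but it does not call the design or the sample size into question.

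**What to change.** In section 7.5:

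1. Name change in PHQ-9 from baseline to 3 months postpartum as the single primary test, at two-sided .05. This is the primary hypothesis in 2.1 and the outcome that 7.2 was sized for.
2. Test the Aim 2 primary hypothesis as confirmatory only if that test is significant, at two-sided .05, following the order in 1.1.1. Its time point must be settled at the same time, because 2.1 uses the third trimester and 7.5 uses 3 months postpartum.
3. State that the secondary hypotheses are supportive, reported with estimates and confidence intervals, and not controlled for multiplicity.

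In the Study Schema, list person-centered care under the secondary aim, in line with 1.1.1, and add a sentence to 2.1 saying that its primary hypothesis is primary within Aim 2 only.

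The cost is a few sentences. Enrollment stays at 657 and Aim 1 keeps 85% power. The one real downside is that Aim 2 cannot be claimed as confirmatory if Aim 1 fails. If the sponsor wants both aims to stand as primary, the plan should say so and state how alpha is divided, with the loss of power shown above.

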### 2.1 Hypotheses

The first aim of the study is to compare the effect of *Glow group prenatal care with wrap around services (Glow/GC) versus individual prenatal care with supplemental services covered by the California Department of Public Health Comprehensive Perinatal Services program (CPSP/IC)* on changes in depressive symptom severity (1° outcome) and anxiety symptom severity (2° outcome) from baseline (6-24 weeks gestation) to postpartum (3 months), using the Patient Health Questionnaire (PHQ-9) and the Generalized Anxiety Disorder (GAD-7) scale. The hypotheses for this study aim are:

#### Primary Hypothesis (Aim 1)

- Compared to women allocated to CPSP/IC, women allocated to Glow/GC will have greater reductions in baseline depressive symptom severity at 3 months postpartum.

#### Secondary Hypotheses (Aim 1)

Compared to women allocated to CPSP/IC, women allocated to Glow/GC will have:

- Greater reductions in baseline depressive symptom severity in the 3rd trimester.

- Greater reductions in baseline anxiety symptom severity at 3 months postpartum and in the 3rd trimester.

The second aim is to compare the effect of Glow/GC and CPSP/IC on participant-reported person-centered care, measured with Person-Centered Prenatal Care scale (PCPC) and Person-Centered Maternity Care scale, respectful care measured with Mothers on Respect index (MORi), and satisfaction with care, measured with Prenatal Care Satisfaction (PCS) scale.

#### *Primary Hypothesis (Aim 2)*

- Compared to women allocated to CPSP/IC, women allocated to Glow/GC will report more person-centered care in the 3rd trimester.

#### *Secondary Hypotheses (Aim 2)*

Compared to women allocated to CPSP/IC, women allocated to Glow/GC will report:

- More person-centered care at 3 months postpartum.
- More respectful care in the 3rd trimester.
- More satisfaction with care in the 3rd trimester and at 3 months postpartum.

The third aim is to compare the effect of Glow/GC versus CPSP/IC on preterm birth rates and gestational age at delivery among low-income women. This is an exploratory aim.

#### *Exploratory Primary Hypothesis (Aim 3)*

- Compared to women allocated to CPSP/IC, women allocated to Glow/GC will have lower rates of preterm birth.

#### *Exploratory Secondary Hypotheses (Aim 3)*

- Compared to women allocated to CPSP/IC, women allocated to Glow/GC will give birth at higher gestational ages.

## **2.2 Study Design**

This is a randomized comparative effectiveness trial to determine the effect of two enhanced prenatal care models, Glow/GC and CPSP/IC, on depressive and anxiety symptom severity; person-centered care, perceptions of respectful care, and satisfaction with prenatal care; and PTB rates and gestational age at delivery among 657 birthing people. Providers will be randomized to the order in which they offer the two models, and participants will be allocated to each of the comparators based on their provider and expected due date. Providers may select the mode of comparator delivery—either in person, via telehealth or a combination of both—according to personal preferences, health center regulations, and local public health guidelines. A CONSORT diagram of the study is presented as Figure 2.

## **2.3 Randomization**

Both comparators will be offered within each site. At each site, participating providers will be randomly assigned to one of two recruitment tracks: recruiting initially for Glow/GC or recruiting initially for CPSP/IC. The two tracks will alternate between recruitment for Glow/GC and recruitment for CPSP/IC based on prespecified six-week ranges of estimated delivery dates (EDD), for the duration of the study. Based on the provider's randomization track and the participant's due date, participants will be placed in either the Glow/GC or CPSP/IC arm (see Figure 3 for an example of the treatment assignment for Provider A, who was randomly assigned to recruit for Glow/GC for the initial 6-week period of the study). This design optimizes the number of Glow/GC sessions offered by each practice (no more than 4 concurrent groups per clinician) and is ideal for clinic flow. Because the maximum number of women

who can be enrolled in a Glow cohort is 12, after 12 have enrolled, subsequent eligible women will be allocated to CPSP.

Figure 2. Consort diagram

[figure not shown]

Randomization will be stratified by recruitment site and provider. If the site has more than one provider and can accommodate only one Glow group at a time, the first provider will be randomized to a starting comparator track and the second provider will start with the other comparator sequence. Randomization tables were generated in blocks of size 4 with Stata v16.0 using the runiform function, which utilizes the 64-bit Mersenne-Twister random number generator. RRSs will not assign participants to the Glow/GC or CPSP/IC arm until after completion of their baseline survey, at which point the RRS will inform the participant of her group assignment and enter it into the study database. The appropriate comparator assignment is determined utilizing a tool that does not reveal comparator

estimated due date ranges. To help ensure that the assessors of the primary and secondary outcomes are masked with respect to group assignment, a different staff member will conduct the third trimester and postpartum interviews and perform the medical chart abstraction.

**Figure 3. Example Provider Recruitment Track with Randomization**

[figure not shown]

### 3.0 STUDY POPULATION

A total of 657 pregnant women who are between 8 weeks (or less than 8 weeks with pregnancy confirmed by ultrasound) and 24 weeks gestation and eligible for Medi-Cal will be enrolled into the study from one of the participating prenatal care provider sites in Fresno County. Fresno County has the highest rate of preterm birth in California and a high rate of poverty among pregnant women. Provider sites in Fresno County are staffed by obstetrician-gynecologists, family medicine physicians, physician assistants, nurse-midwives, nurse practitioners, nurses, and other health care providers. Together, these sites serve a diverse patient population, both racially/ethnically and linguistically, and primarily consist of Medi-Cal recipients, similar to low-income care settings across the US.

Providers will be randomized to offer Glow/GC or IC/CPSP in 6-week intervals, and participants will be assigned to the intervention based on their due dates. Participants will be selected for the study according to the criteria in Sections 3.1 and 3.2. They will be approached, screened, and enrolled as described in Sections 5.1.1., 5.1.2., and 5.1.3. Issues related to participant retention and withdrawal from the study are described in Sections 3.3 and 3.4, respectively.

#### 3.1 Inclusion Criteria

Women who meet all of the following criteria are eligible for inclusion in the study:

- ≤24 weeks, 6 days' gestation (with pregnancy confirmed by ultrasound if < 8 weeks) at enrollment
- Eligible for Medi-Cal (at or below 213% of the federal poverty level)
- Speak English or Spanish
- Willing to be assigned to Glow/GC or CPSP/IC to receive prenatal care

#### 3.2 Exclusion Criteria

Women who meet any of the following criteria will be excluded from this study:

- Not planning to continue prenatal care with site provider
- Cannot legally consent to participate in the study
- Unable to speak the language of the sessions that are meeting
- Unable to attend group prenatal care session at the scheduled time

### 3.3 Participant Retention

Once a participant enrolls in EMBRACE, every effort will be made to retain them in the study for the entire follow-up period to minimize possible bias associated with loss to follow-up. Components of such procedures may include:

- Thorough explanation of the study interview schedule and procedural requirements during the informed consent process.
- Collection of email, phone, and address contact information during enrollment.
- Collection of an alternative contact's email and phone information after the consent process.
- Repeated contact attempts to schedule interviews.
- Immediate follow-up for missed interviews.
- Email and physical mail reminders.
- Retention gift sent by mail prior to the final interview.
- In-person approach at participant's prenatal care site if the participant cannot be reached through email, phone, or physical mail.

Contact attempts: RRSs will attempt to contact the participant up to 5 times and will record all contact attempts in the REDCap database. After the fifth attempt, the RRS will reach out to the alternative contact. If attempting to reach the alternative contact does not result in contact with the participant, the RRS will attempt to get updated contact information from clinic staff. If the previous methods are all unsuccessful, the RRS will report the participant as lost to follow-up in the REDCap database on the "discontinuation, withdrawal, and loss to follow-up" form.

### 3.4 Participant Withdrawal

Participants who withdraw from their assigned intervention will be encouraged to complete all study questionnaires. Cards and a retention gift will be sent to promote study engagement. However, regardless of the participant retention methods used, participants may voluntarily withdraw from the study for any reason at any time. Participants also may be withdrawn if the study sponsor, regulatory authorities, or site IRB terminate the study prior to its planned end date.

The study team will evaluate participants withdrawn from the study on a case-by-case basis to determine whether birth outcomes may be collected from the chart and retained in analyses. A final determination will be made according to a participant's stated preference for use of her medical record data and the data use guidelines set forth in the informed consent form.

## 4.0 STUDY ARMS

### 4.1 Glow/GC (enhanced group prenatal care, eGPC)

Glow/GC, Comparator 1 for this study, is an enhanced group prenatal care program administered by First 5 Fresno County that offers co-located social services provided by established community agencies with independent funding streams targeting low-income families. The Glow/GC model pairs a trained staff facilitator with a licensed prenatal care provider from a practice site to provide billable prenatal care to the practice's own patients. Over the course of 8-11 sessions, 6-12 women (within a 6-week gestational age range) receive prenatal and postpartum medical care, risk assessments, social support, and gain knowledge and skills related to pregnancy, birth, and parenting. Glow/GC modifies the CenteringPregnancy®69 curriculum, which incorporates ACOG recommendations for prenatal

care, to include modules focusing on depression, anxiety, sleep, mindfulness, and how discrimination may affect birth outcomes. Spanish-language sessions and materials are available.

Additional Glow program components include childcare support with developmental assessments (in-person model) or in-home early learning activities for children ages 0 to 5 (telehealth model); education, referral, and treatment for perinatal mental health issues and conditions administered by the Department of Behavioral Health, Perinatal Wellness Program (both models); transportation stipends (both models); take-home food (in-person model) or food delivery (telehealth model) through local food banks and other community agencies; and direct coordination/enrollment with education, housing, economic assistance, and other local services as needed (both models). Glow/GC staff maintain a county-based, low-income resource guide and work continuously to build relationships and facilitate warm handoffs.

The current protocol incorporates the needs identified by participants, community members, and stakeholders who shared their feedback regarding telehealth modifications to meet required physical distancing and other challenges presented by the COVID-19 pandemic. The core components of Glow! sessions were retained and modified to fit the abilities of participants and providers to use telehealth. First 5 Fresno County manages the Glow/GC program and closely documents any changes to their program protocol and implementation. The EMBRACE project manager and project specialist will work closely with the agency to track these changes and communicate them to the rest of the EMBRACE team.

